**Fig. 1 Fig1:**
[figure not shown]
Survey dates of HRQoL, satisfaction, time and distance

### Sample size

As the study initially pursues the general proof of concept and has an observational character, it aims to explore complex interactions and the evolution of the use of VaO rooms rather than to quantify specific instances. We see the development of the usage of the VaO rooms, the number of patients receiving care and the given services as indicators of study success. The sample size estimation is conducted using the tool G*Power Version 3.1.9.7 of Heinrich Heine University of Düsseldorf. The calculation is based on an expected effect size of 0.25, an alpha error level of 0.05 and a statistical power of 0.80. Given the repeated measures ANOVA design, the number of groups is set to one with three measurement time points. Additionally, a correlation of 0.5 between repeated measures is assumed, and the nonsphericity correction is set to the default value of one. This results in a required total sample size of 28, with an actual power of 0.81.

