### Trial design

The study is designed as a non-randomised, single-arm longitudinal observational study with repeated measurement points in the context of health services research. It is conducted from January 2023 to June 2025, spanning a total duration of 30 months and comprising five phases. The first one, the preparatory phase focused on the requirements of implementation. These were assessed by participating GPs and selected according to the following criteria: (1) village where home visits are carried out (2), number of patients receiving home visits, and (3) share suitable for visiting a VaO room. Suitable premises were selected in collaboration with local mayors. A checklist in accordance with the Association of General Practitioners in Germany (VirchowBund) was used to ensure alignment of the facilities [15]. The criteria included, for example, accessibility, sanitary facilities and stable internet connections. The rooms were inspected by HPs and GPs.

In the initial assessment and testing phase, patients’ care in VaO rooms by their known HPs starts. The HPs continuously monitor the patients’ state of health to determine their suitability for care in VaO rooms [16]. The subsequent interim evaluation and concept adjustment phase aims to correct weaknesses, sources of risk and errors from the initial assessment and testing phase by conducting a focus group interview with the participating HPs on their satisfaction with the use of the room. Sources of risk and errors are targeted while adjustments to the VaO concept optimise processes. In the second survey phase, the time and distance parameters of patient care are continuously collected. A final evaluation is carried out at the end of the study to test the hypotheses.

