### Intervention description

After being selected by the participating GPs and providing informed consent, patients receive their medical care through delegated services in one of the established VaO rooms during all phases of the study as long as they meet the inclusion criteria. They receive the same care as if they were at home – the range of services provided by HPs is not extended, only the location of the service changes. For instance, services such as the collection of blood samples, the measurement of blood sugar levels or the treatment of wounds may be provided at the VaO rooms. The HP-patient relationship remains the same as well, as the HPs continue to see the same patients they have seen in their home visits.

The use of the VaO rooms is organised independently of the practices. This means that presence times and patient timing are managed by the HPs themselves so that the VaO rooms can be individually integrated into practices’ daily routine. For example, the frequency of opening the VaO room or the type of patient appointment can be determined by the practices. This concept is based on continuity, as the combination of GP, HP, patients and services remains unchanged. This makes it possible to change the location of care provision without interfaces and without loss of any information.

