### Statistical methods

#### Statistical methods for primary and secondary outcomes

Table 1 shows the statistical methods used to analyse quantitative data.

**Table 1 Tab1:** Statistical methods used for quantitative data sets

Data	Points in time	Statistical method
SF- 12	t0, t1, t2	Descriptive statistics, paired t test, ANOVA with repeated measures
ZUF- 8	t0, t1, t2	Descriptive statistics, paired t test, ANOVA with repeated measures
Kilometers	continuous	Descriptive statistics, paired t test, Wilcoxon test
Time	continuous	Descriptive statistics, paired t test, Wilcoxon test

The baseline data (t0) on HRQoL and patient satisfaction are analysed using descriptive statistics. To assess the changes that occurred after the first survey and testing phase, data collected at t0 and t1 are compared using paired t-tests or Wilcoxon test as part of an interim analysis. Upon completion of the second survey and testing phase, all data from the three measurement points (t0, t1 and t2) are subjected to a repeated measures ANOVA to compare outcomes across all three time points.

Additionally, the distance travelled and time spent are compared between the VaO scenario and the home visit scenario. Given the conditions shown, paired t tests or Wilcoxon test are used to determine whether there are any discernible differences in the parameters under examination.

The emphasis is on understanding underlying trends, patterns and on gaining real world evidence.

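### The sample size of 28 is a number of patients complete at t0, t1 and t2 and allows for no missing questionnaires, although the protocol's own care rules and calendar make missing t1 or t2 values likely

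*Protocol article*

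**What the plan says.** The Sample size section describes a G*Power calculation for one group: "The calculation is based on an expected effect size of 0.25", "an alpha error level of 0.05" and "a statistical power of 0.80"; "the number of groups is set to one with three measurement time points". The correlation between repeated measures is 0.5 and the nonsphericity correction is 1. The section concludes: "This results in a required total sample size of 28, with an actual power of 0.81". It lists no attrition term and does not say whether 28 means enrolled or complete.

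The statistical methods section names the final analysis of HRQoL and satisfaction: the data from t0, t1 and t2 are "subjected to a repeated measures ANOVA to compare outcomes across all three time points".

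Three other places bear on who will have all three measurements:

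- **Care in the room.** The Intervention description says that patients are treated "in one of the established VaO rooms during all phases of the study as long as they meet the inclusion criteria". Under Eligibility criteria, one of these is being able to visit the room. The Trial design section adds "The HPs continuously monitor the patients", meaning their state of health, to judge whether they remain suitable for the room.
- **Calendar.** Patient recruitment admits patients enrolled up to 31 July 2024 to the HRQoL and satisfaction analysis, so that t0 to t1 can be followed. The Outcomes section puts t2 at 12 months. Trial design ends the study in June 2025.
- **Hypothesis.** Hypothesis 3 under Objectives is that HRQoL does not change.

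**The concern.** The error degrees of freedom behind the stated power exist only if 28 patients have all three measurements. The patients are older people on home visits, followed for 12 months, and the protocol provides for their leaving room care when they can no longer come. Those who leave for that reason are likely to have worsened, and worsening is what the SF-12 measures.

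Two things are at stake. First, precision: each patient dropped from the ANOVA takes the analysis below the power quoted. Second, direction: because Hypothesis 3 is one of no change, low power and selective loss of declining patients both push towards the result that favours the concept. The primary outcomes, travel and setup time, do not depend on this calculation.

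**Working it through.** **Step 1: reproduce the stated figure.** Inputs from the Sample size section: f = 0.25, alpha = 0.05, m = 3 time points, rho = 0.5, epsilon = 1. For a within-subject factor, power comes from the noncentral F distribution with

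- lambda = f² × N × m × epsilon / (1 − rho)
- df1 = (m − 1) × epsilon
- df2 = (N − 1)(m − 1) × epsilon

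For N = 28: lambda = 0.0625 × 28 × 3 / 0.5 = 10.5, df1 = 2, df2 = 27 × 2 = 54, power 0.812. For N = 27: lambda = 10.125, df2 = 52, power 0.796. So 28 is the smallest N that reaches 0.80, and the stated figures are correct. The value df2 = 54 presupposes 28 patients with all three measurements; one incomplete patient takes power just below 0.80.

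**Step 2: power with fewer complete patients.** The documents give no loss rate, so 10% to 30% is an assumption. This step also assumes that exactly 28 are enrolled and that loss is random.

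| Assumed loss | Complete patients | Power | Enrolment that keeps 28 complete, 28/(1 − d) |
|---|---|---|---|
| 0% | 28 | 0.81 | 28 |
| about 10% | 25 | 0.76 | 32 |
| about 20% | 22 | 0.70 | 35 |
| about 30% | 20 | 0.65 | 40 |

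**Step 3: calendar.** Enrolment in July 2024 plus 12 months is July 2025. The study ends in June 2025. For these patients t1 falls within the study and a 12-month t2 does not. This source of missing t2 values has nothing to do with health.

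**Step 4: direction and possible size of bias under health-related loss.** The loss mechanism is assumed throughout.

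- *Graded loss, simulated (20,000 runs per scenario).* 28 enrolled, complete cases only, a true linear decline of 0.61 SD from t0 to t2 (what f = 0.25 implies for a linear pattern: 0.25/√(1/6) = 0.612), 20% lost. Random loss: observed decline 0.61 SD, power 0.70. Loss related to a low t2 score: 0.49 SD, power 0.51. Loss related to the decline itself: 0.36 SD, power 0.33.
- *Worst case, by formula.* Suppose exactly the lowest 20% of t2 scores are missing. The observed t2 mean rises by phi(0.842)/0.8 = 0.35 SD, and the t0 mean of the same patients by 0.5 × 0.35 = 0.175 SD. The apparent change is therefore shifted upwards by 0.35 − 0.175 = 0.175 SD, and a true decline of 0.30 SD appears as 0.125 SD. With the lowest 10% missing, the t2 shift is phi(1.282)/0.9 = 0.195 SD and the decline appears as about 0.20 SD.

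**Step 5: does a mixed model cure this?** Take the worst case of step 4, with an assumed t1 decline of 0.15 SD and only t2 missing. For a true decline of 0.30 SD, a likelihood-based model on all available data estimates 0.03 SD when the lowest 20% are missing, against about 0.12 SD from complete cases. With the lowest 10% missing it estimates 0.16 SD, against 0.20 SD. When loss is set by the unseen score, the data are not missing at random and the model is further from the truth. It does keep the patients of step 3, whose t2 is missing for calendar reasons.

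**The case against.** A reader might infer that the stated power will not be reached and that the ANOVA will hide a decline in HRQoL. The documents do not support either statement as fact.

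- **Enrolment is not capped at 28.** With 35 enrolled and 20% lost, 28 remain and the stated power is kept. Against this, the Discussion expects relatively few participants, so a surplus cannot be presumed.
- **Leaving the room is not leaving the survey.** The continuation rule governs where care is given. Nothing stops the SF-12 or ZUF-8 when a patient returns to home visits; the data collection section has participating patients answer at all three times and adapts the ZUF-8 to either setting. Follow-up may already be intended, but it is not stated for patients who leave the room.
- **Complete-case handling is not stated.** It is the usual consequence of the classical ANOVA named, and missing-data rules may stand in an analysis plan that is not shown. The paired t0 to t1 comparison still uses a patient who misses only t2.
- **The bias sizes rest on assumptions.** Removing exactly the worst t2 scores is an extreme case. With a true decline of 0.61 SD, the same 20% truncation leaves 0.61 − 0.175 = about 0.44 SD.
- **The outcomes are secondary**, and the article already declines to attribute HRQoL changes to the concept.

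These points stand and make the power loss and the bias conditional. They do not change the published calculation, which lists its inputs and has no allowance for loss, or the calendar, which leaves no room for a 12-month t2 in the last patients admitted.

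**Conclusion.** The point holds in conditional form. N = 28 with power 0.81 is arithmetically right, but it describes patients complete at t0, t1 and t2, for the secondary outcomes only, with no margin: 27 complete patients give 0.796. The protocol itself contains two routes to missing values, one linked to health and one to the calendar.

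Power of 0.76, 0.70 or 0.65 follows if only 28 are enrolled, about 10%, 20% or 30% are lost at random, and incomplete patients are dropped. Understatement of a decline follows if questionnaires stop or go unanswered after a worsened patient leaves the room. Its direction favours Hypothesis 3; its size is unknown and depends on the loss mechanism assumed. The change should be made, but the primary outcomes are not affected.

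**What to change.** 1. State that SF-12 and ZUF-8 are collected at t1 and t2 from every enrolled patient, including those back on home visits. This is the step that addresses health-related loss.
2. Replace the repeated-measures ANOVA with a linear mixed model: time as a factor, unstructured covariance, all available data. It keeps patients with a missing t2, including those who miss it for calendar reasons. It does not remove bias if loss depends on the unseen score, so add a sensitivity analysis that assumes worse scores for those lost.
3. Restate the figure as *28 patients complete at t0, t1 and t2, for the secondary outcomes*, and give the power at smaller complete numbers, for example 0.70 with 22.

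The cost is a few more questionnaires, a standard model with one sensitivity analysis, and a less favourable power statement. If recruitment has closed, the model, the sensitivity analysis and the restated figure remain possible.

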### Data collection and management

#### Plans for assessment and collection of outcomes

##### Patient satisfaction and HRQoL

The participating patients are administered the SF- 12, a questionnaire frequently used in clinical studies, to assess their HRQoL. Additionally, the ZUF- 8, a questionnaire designed to assess patient satisfaction, is used after being adapted to the context of the “home visit” or “VaO” setting. Both questionnaires are completed at three points in time (t0 before the first VaO room visit of the patient, t1 after six months, t2 after 12 months) during the course of the study to observe and evaluate changes.

In addition, focus group interviews will be conducted with the participating HPs on their satisfaction with VaO concept at survey times t1 and t2. Therefore, we designed an interview guideline which covers important objects like time saving or the changes due to the use of VaO in everyday working life (Appendix A). The interviews are intended to capture the range of opinions of the HPs regarding the innovative VaO concept in an open discussion to validate or question its components. Additionally, potential success factors or barriers to the implementation of the concept will be identified.

##### Time and distance savings

As part of the initial data collection and testing phase, distances travelled are continuously monitored and collected for two scenarios: the VaO scenario, in which all eligible patients are cared for in VaO rooms; and the home visit scenario, in which all patients are cared for at home. The online route planner MapQuest is used to calculate the optimal routes for each of the scenarios, with the results presented in the form of distance and time estimates [20]. In addition to the abovementioned measures of time spent away from the patients, the setup times (preparation and follow-up of materials) for services performed during the home visit were measured before the beginning of the study with the participating HPs. These setup times are also included in the evaluation of time savings.

##### Costs

The costs of the innovative form of care are calculated using the existing remuneration models for medical assistants in job group IV of the German Collective Labour Agreement for Medical Assistants. The average salary and the average monthly working time of a full-time HP are calculated using the collective agreement for medical assistants of the Bavarian Medical Association [21, 22]. The exact values are one basis for calculating the expected cost savings from VaO.

To measure the cost-effectiveness of the intervention, the incremental cost-effectiveness ratio (ICER) of the innovative care system VaO in comparison to the standard method of care is calculated. Mathematically, the ICER sets the difference in costs in relation to the difference in benefits and allows to illustrate the drivers and limitations (e.g., effects of VaO room utilisation, logistical challenges) of cost-effectiveness:

$$\mathrm{ICER}\;=\;({\mathrm C}_{\mathrm{VaO}}-{\mathrm C}_{\mathrm{standard}})/({\mathrm B}_{\mathrm{VaO}}-{\mathrm B}_{\mathrm{standard}})$$

C_VaO_ includes the calculated costs of the care system VaO, namely, room rent (including maintenance and cleaning), which is calculated from the local standard comparative rent, as well as the costs of travel distances and times according to the VaO route planning when using the VaO rooms.

C_standard_ includes the cost of travel distances and times according to standard route planning.

B_VaO_ includes the benefit expressing change in satisfaction and HRQoL from t0 to t1 and t2 as mentioned above as a reflection of the satisfaction with the innovative form of care.

B_standard_ includes the benefit expressing average HP and patient satisfaction at time t0, reflecting satisfaction with their usual form of care.

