Several delegation concepts exist and aim to reduce the workload of GPs, such as different types of specialised care assistants, ‘care assistants in the GP practice’ (VERAH), ‘nonphysician practice assistants’ (NäPA) or ‘physician-supported, community-based, e-health-supported, systemic intervention’ (AGnES)- hereafter referred to as healthcare professionals (HPs). These specially trained HPs can carry out defined activities delegated by GPs, including home visits. This frees up GP time for patient care, especially in rural areas with long distances to and between patients’ homes [13].

The delegation of GPs’ activities is therefore a promising strategy to address care gaps. However, the availability of delegation recipients is also finite. To maximize the efficiency of healthcare services, it is crucial to optimise the organization of service provision. The VaO concept addresses this by relocating home visits to nearby, well-equipped VaO rooms for patients who are physically able to access them. These rooms serve as treatment centers used exclusively by healthcare professionals (HPs) and patients with GP recommendations. Within the VaO care model, the scope of services and the HPs delivering them stay as they are established, medical management remains under GP supervision. Services provided include measuring blood sugar levels, changing dressings, or taking blood samples, as defined by the Agreement on the delegation of medical services to nonmedical staff in outpatient care of contract physicians care in accordance with § 28 Para. 1 S. 3 SGB V by the Association of Statutory Health Insurance Physicians in cooperation with the National Association of Statutory Health Insurance Funds [14].

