## Objectives

The overall aim is to (1) implement the VaO concept in a real-world setting in the Streutal Valley in Northern Bavaria and to (2) evaluate its effectiveness by assessing economic efficiency, satisfaction and HRQoL in compared to the usual care provision.

Therefore, the primary objective is to conduct a health economic evaluation of VaO as a minor modification and resource-saving interdisciplinary form of care to mitigate the shortage of GPs in rural areas. The secondary objective is to test its feasibility and integration into the daily routines of patients, HPs and GPs as well as to evaluate the psychosocial effects of the concept. The following hypotheses are being tested to answer the selected research question.

Hypothesis 1: The monetary expenses and savings of the VaO care model lead to economically neutral to positive results for the GPs running the rooms.Hypothesis 2: The VaO care model reduces average working time spent in nonpatient areas (travel and setup time).Hypothesis 3: The VaO concept does not lead to a change in patients’ HRQoL.Hypothesis 4: The VaO concept does not lead to a change in patients’ and HPs satisfaction.

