### Study setting

The study is being conducted in VaO rooms, which have been specially set up for this purpose. The rooms are furnished and aligned in accordance with criteria of the VirchowBund for medical practices [15]. There are seven VaO rooms located in the villages of Stockheim, Oberstreu, Hendungen, Hausen, Oberwaldbehrungen, Unsleben and Bastheim in the bavarian region Streutal. In the initial assessment and testing phase, those are used and shared by three practices, of which two are joint practices.

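### The ICER cost terms price neither setup time, which is part of the primary outcome, nor the furnishing and equipping of the VaO rooms

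*Protocol article*

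**What the plan says.** All references are to the protocol article.

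- **Costs, VaO term.** C_VaO is introduced as "namely, room rent (including maintenance and cleaning), which is calculated from the local standard comparative rent". The only further item is travel by HPs, with distance and time both taken from the routes planned for VaO.
- **Costs, standard term.** C_standard "includes the cost of travel distances and times according to standard route planning".
- **Costs, wage basis.** HP salary and monthly working time are taken from a collective agreement, and of these it is said: "The exact values are one basis for calculating the expected cost savings from VaO".
- **Objectives.** The primary objective is a health economic evaluation. Hypothesis 1 reads: "The monetary expenses and savings of the VaO care model lead to economically neutral to positive results for the GPs running the rooms". Hypothesis 2 concerns working time away from patients and names travel and setup time.
- **Outcomes.** The primary outcome is time saved in travel and setup.
- **Time and distance savings.** Travel distance and time come from an online route planner. Setup times were measured separately with the HPs, for services given on home visits, before the study began. "These setup times are also included in the evaluation of time savings".
- **Background and Study setting.** The model means "relocating home visits to nearby, well-equipped VaO rooms". There are seven such rooms, "which have been specially set up for this purpose" and furnished to criteria for medical practices.

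**The concern.** The resources that the article describes and the resources that it prices do not match, in two places.

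First, a route planner returns driving distance and driving time. It cannot return the minutes spent preparing and clearing away materials. Both cost terms take time from route planning alone, so setup time counts as a benefit in the primary outcome but has no value in the cost comparison.

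Second, the contents of the rooms are a resource that exists only under VaO. The VaO list covers the premises and the journeys but not what was put into the rooms.

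At stake is the numerator of the ICER, which is the only cost comparison described for the primary objective. If the true net difference is near zero, either omission could change its sign.

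**Working it through.** **The plan's own figure.** The article states no cost result, so there is none to reproduce. The check compares the listed cost items with the resources described, and then works out the direction of each omission.

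**Side by side**

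| Resource | Described in | In C_VaO? | In C_standard? |
|---|---|---|---|
| Room rent, maintenance, cleaning | Costs | yes | not applicable |
| Travel distance and time | Costs; Time and distance savings | yes | yes |
| Setup time | Objectives; Outcomes; Time and distance savings | no | no |
| Furnishing and equipment of seven rooms | Background; Study setting | no | not applicable |

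**Direction.** Let R be yearly rent, w the HP hourly wage, k the cost per kilometre, T travel hours, D kilometres, S setup hours, F the one-off furnishing and equipment cost, and L the write-off period in years.

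- As written: C_VaO − C_standard = R + w(T_VaO − T_std) + k(D_VaO − D_std).
- With the missing items: the same, plus F/L + w(S_VaO − S_std).
- Error in the written difference: F/L + w(S_VaO − S_std) is left out.

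F/L cannot be negative, so leaving it out understates the cost of VaO. The setup term is negative if the rooms save setup time. Leaving it out then works against VaO. If setup takes longer in the rooms, the omission favours VaO.

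**Illustration.** Only the seven rooms and the 30-month study duration come from the article. Every price and minute below is an assumption.

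- Furnishing and equipment at EUR 1,000 to 10,000 per room gives F = 7 × 1,000 to 7 × 10,000 = EUR 7,000 to 70,000.
- Written off over 5 years: EUR 1,400 to 14,000 per year.
- Written off over the 30 months (2.5 years) of the study: EUR 2,800 to 28,000 per year.
- Setup time saved of 2 to 5 minutes per service at EUR 18 to 26 per hour: 2/60 × 18 = EUR 0.60 up to 5/60 × 26 = EUR 2.17 per service.
- Services per year at which the two omissions cancel: from 1,400/2.17 ≈ 645 to 28,000/0.60 ≈ 46,700.

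The article gives no number of services. A break-even range this wide means that the sign of the net error cannot be settled from the document.

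**The case against.** Five arguments can be made for the plan.

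1. **Setup time may be priced elsewhere.** The wage values are called one basis for the expected savings, and setup times are included in the evaluation of time savings. Multiplying the two is a natural step. This stands in part: a reader might infer that the economic evaluation ignores setup time altogether, and the article does not support that. It supports only that the two ICER cost terms, as defined, do not include it.

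2. **Hypothesis 1 is not tied to these terms.** They are introduced for the ICER. No sentence says that Hypothesis 1 is decided on C_VaO minus C_standard. This stands: the link is an inference, although no other cost comparison is described.

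3. **The GPs may not have paid for the furnishing.** Hypothesis 1 takes the view of the GPs running the rooms, and the article does not name the payer. This stands, and it defeats the tempting reading that the omission biases Hypothesis 1 towards success. It does not rescue the ICER, whose VaO term is described as the cost of the care system. Rent there is valued at a comparative market rate, and no reason is given for valuing the premises but not their contents.

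4. **Internet connection.** A reader might add a separate charge for connecting the rooms. Trial design mentions stable internet only among the criteria for suitable premises, so the article shows no such charge.

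5. **A condensed article leaves cost inventories to fuller documents.** That would excuse missing unit prices and write-off periods. It does not excuse the terms themselves: the article writes out the formula, introduces the VaO items as a specific list and goes down to cleaning. The standard-care list is worded more loosely, but it too refers only to route planning.

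**Conclusion.** The point holds for the ICER. As defined, its cost difference omits setup time, which is half of neither a stated total nor a known amount but is one of the two named components of the primary outcome. It also omits furnishing and equipment that only VaO requires. The setup-time omission is an inconsistency within the article and does not depend on who pays. The furnishing omission understates the cost of the care model.

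For Hypothesis 1 the conclusion is weaker. A bias there requires that the hypothesis is judged on this cost difference and, for the furnishing part, that the GPs bear the cost. The article states neither.

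No corrected figure can be given, because the rent, wage, equipment prices, setup minutes and number of services are not in the document. The euro amounts above show only what plausible inputs would imply. The two omissions can offset each other, so the net error has no known sign.

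**What to change.** In Costs:

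- Add setup time to both C_VaO and C_standard, priced at the same HP wage rate as travel time. For home visits, use the setup times already measured. For the VaO rooms, the article describes no such measurement, so take one or state an assumed value.
- Add the annualised furnishing and equipment cost of the seven rooms to C_VaO, with the write-off period stated.
- Report the cost difference and the Hypothesis 1 result with and without furnishing and equipment.
- State whose costs are counted, who bore the furnishing and equipment cost, and which cost difference decides Hypothesis 1.

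The price is a little more costing work and possibly a short measurement of setup time in the rooms. The reported saving may become less favourable.

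### The ICER denominator subtracts a baseline level from a change score with different components, so the ratio mainly reflects the t0 score; even when corrected it would be unstable if Hypotheses 3 and 4 hold

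*Protocol article*

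**What the plan says.** The Costs section of the protocol article plans an incremental cost-effectiveness ratio of VaO against usual care. It explains that "the ICER sets the difference in costs in relation to the difference in benefits" and writes the ratio as (C_VaO − C_standard)/(B_VaO − B_standard).

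The two benefit terms are then defined:

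- B_VaO "includes the benefit expressing change in satisfaction and HRQoL from t0 to t1 and t2".
- B_standard "includes the benefit expressing average HP and patient satisfaction at time t0, reflecting satisfaction with their usual form of care".

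The Objectives section makes a health economic evaluation the primary objective and states the relevant hypotheses. Hypothesis 1: "The monetary expenses and savings of the VaO care model lead to economically neutral to positive results for the GPs running the rooms". Hypothesis 3: "The VaO concept does not lead to a change in patients’ HRQoL". Hypothesis 4: "The VaO concept does not lead to a change in patients’ and HPs satisfaction".

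The Outcomes section names travel and setup time as the primary outcomes. The section on patient satisfaction and HRQoL has patients complete the SF-12 and ZUF-8 at t0, t1 and t2. For HPs it describes focus groups at t1 and t2 only.

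**The concern.** An incremental benefit compares the same quantity under two forms of care. Here the first term is already a difference from t0 and the second is the t0 score itself, so the baseline is in effect removed twice. The terms also differ in content. HRQoL enters the VaO term and not the standard-care term. The standard-care term asks for an average HP satisfaction at t0, while the only HP assessment described is qualitative and starts at t1.

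If the formula is applied as printed, the reported cost per unit of benefit would be driven by how satisfied patients were before the project began, and it would hardly distinguish a gain from a loss. The ICER is the only cost-effectiveness measure that the article names under its primary objective, so a reader would give it weight.

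**Working it through.** **The plan's own figure.** The article gives no numerical ICER, so the only figure that can be reproduced is the sample size. Inputs from the Sample size section: f = 0.25, alpha = 0.05, power 0.80, one group, three time points, correlation 0.5, nonsphericity correction 1. The noncentrality is f² × N × m/(1 − ρ) = 0.0625 × 28 × 3/0.5 = 10.5, with 2 and 54 degrees of freedom. Power is 0.812 at N = 28 and 0.796 at N = 27. The stated 28 and 0.81 are reproduced, and N = 28 and ρ = 0.5 are used below.

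**Step 1: the denominator as written.** Let L be the mean score at t0 and d the mean change from t0, on one scale.

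- As written: B_VaO − B_standard = d − L.
- Follow-up level minus t0 level: (L + d) − L = d.

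The printed denominator is negative whenever d < L. Its sign is therefore wrong for any gain smaller than the baseline score. For a loss the sign is right and only the size is wrong.

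**Step 2: size of the error.** The documents give neither L nor the cost difference. Assume C_VaO − C_standard = −1,000 EUR and L = 20, 25 or 30 points.

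| Change d | As written, L = 20 | L = 25 | L = 30 | Denominator d |
|---|---|---|---|---|
| −2 | −1000/−22 = +45.5 | −1000/−27 = +37.0 | −1000/−32 = +31.25 | −1000/−2 = +500 |
| 0 | −1000/−20 = +50.0 | −1000/−25 = +40.0 | −1000/−30 = +33.3 | undefined |
| +2 | −1000/−18 = +55.6 | −1000/−23 = +43.5 | −1000/−28 = +35.7 | −1000/+2 = −500 |

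At L = 25, going from a 2-point loss to a 2-point gain moves the printed ratio only from +37.0 to +43.5. With no change at all, moving L from 20 to 30 takes it from +50.0 to +33.3. The baseline dominates. A saving with a gain, which is dominance, appears as cheaper but less effective. The reversal does not depend on the saving: with an extra cost of 1,000 EUR and a 2-point gain at L = 25, the formula gives +1000/−23 = −43.5 instead of +1000/2 = +500.

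**Step 3: the corrected denominator under the trial's own hypotheses.** With level minus level, the denominator is the mean change, whose expected value under Hypotheses 3 and 4 is 0. At N = 28 complete pairs and ρ = 0.5 its standard error is SD × √(2(1 − 0.5))/√28 = SD/5.29 = 0.189 SD. One million simulated draws, with a fixed cost difference of −1 unit, gave:

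- True change 0: denominator negative in 50% of draws and within 0.05 SD of zero in 21%. The middle 95% of ratios ran from about −84 to +85 units per SD.
- True change 0.25 SD: denominator negative, so of the wrong sign, in 9% of draws.

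**Step 4: what does not use the denominator.** Travel time and setup time are compared between two scenarios. Hypothesis 1 needs C_VaO − C_standard. Neither contains a benefit term.

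**The case against.** The intended meaning can largely be recovered. The formula is introduced as a difference in benefits, B_VaO is glossed as reflecting satisfaction with the new form of care, and B_standard as satisfaction with the usual form. A contrast of t1 or t2 with t0 is the likely intent, and an analyst might never compute a denominator of −25. That is fair, but the text says change, nothing elsewhere corrects it, and Step 3 applies to the charitable reading.

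Hypotheses 3 and 4 are propositions to be tested, so the observed change need not be zero, and ways of reporting a ratio with a small denominator are commonly left to an analysis plan. This stands. The instability is therefore a secondary reason to keep the ratio out of the lead role, not a second error in the text.

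A reader might infer more than the documents support:

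- *That the primary analysis fails.* The primary outcomes are times, Hypothesis 1 is a monetary balance, and Table 1 does not list the ICER. None of these depends on the benefit terms.
- *That the sign is always wrong.* It is wrong for gains below the baseline level. For a loss the sign is correct.
- *That HP satisfaction is missing from B_VaO.* That term says satisfaction without qualification, and Hypothesis 4 covers HPs. The clear gap is the t0 value needed in B_standard.
- *That the ratio must be replaced by cost-minimisation or net benefit.* The first would need a non-inferiority margin and the second a money value per point. The documents give neither.

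**Conclusion.** The concern holds for the definition of the denominator. As printed it is d − L instead of d, and its two terms do not contain the same components. The algebra needs no assumption. The sizes do: with a saving of 1,000 EUR and baseline levels of 20 to 30 points, both assumed, no change reads as +50 to +33 EUR per point instead of an undefined ratio. At a baseline of 25, a 2-point gain reads as +43.5 instead of −500 and a 2-point loss as +37.0 instead of +500.

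A corrected ratio would still be unstable if satisfaction and HRQoL stay as Hypotheses 3 and 4 expect. That result rests on 28 complete pairs and the planning correlation of 0.5. The defect is confined to the ICER, which can be corrected with the data already planned and should be corrected before the final evaluation.

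**What to change.** Rewrite the benefit terms in the Costs section:

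1. Define incremental benefit as the follow-up level minus the t0 level in the same patients, on the same instrument. Do this separately for SF-12 physical, SF-12 mental and ZUF-8, and separately for t1 and t2.
2. Remove HP satisfaction from the denominator, since no quantitative t0 measure of it is described. The focus group findings can be reported alongside.
3. State that C_VaO − C_standard, from the perspective of the GPs running the rooms, is the analysis of Hypothesis 1. Show it beside the patient outcomes as a cost-consequence presentation.
4. Label any ICER as supplementary.

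The change is a rewording and needs no further data. Its cost is that there will be no single headline ICER. Preferring a cost-consequence table to a ratio is partly a matter of judgement; items 1 and 2 are not, because without them the ratio is not an incremental one.
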